### Secondary analyses

Secondary outcomes include the key safety outcome of major bleeding (as defined in section N) and the individual outcomes of stroke, systemic embolism, myocardial infarction, and mortality. All secondary outcomes other than major bleeding will use the same analysis approach (primary censoring scheme and regression model) as specified for the primary analysis above. For major bleeding the same regression model as the primary analysis will be used but with the supportive censoring scheme in which patients are censored around the time of last study drug. Within major bleeding results will also be summarised for intracranial, gastrointestinal, and bleeding at other locations. This safety analysis approach will be used for all 3 objectives.

### Sensitivity analyses

All primary and secondary efficacy outcomes described above (stroke/SE combined and individually, MI, and mortality) will also be analysed using the supportive censoring scheme described above in which patients are censored around the time of last study drug. This analysis targets the effect of initiation of apixaban vs initiation or continuation of warfarin on the time to event while on prescribed treatment and investigates whether the extent of treatment discontinuation compromises confidence in the primary and secondary efficacy analyses.

The exclusion of patient-time post initially prescribed treatment discontinuation in the safety and sensitivity analyses might bias the results towards a conclusion of no difference, for example if those at higher bleeding risk were more likely to discontinue one of the treatment arms due to minor bleeding events than if those same minor

[figure not shown]

bleeding events occurred with the other treatment. The set of patients who switch or discontinue treatment during the study period will be examined to ascertain whether biases of this nature have occurred. The proportion of patients switching or discontinuing treatment, timings of withdrawal, and their baseline characteristics will be summarised by initially prescribed treatment.

Additional analyses may be performed using methods such as inverse-probability-of-censoring weighting or a rank-preserving structural failure time model to estimate the treatment effect that would have been observed in the absence of treatment switching.

We expect different adherence in routine clinical practice compared with the trial adherence may explain some of the difference in treatment effect observed between routine clinical care and the trial. Adherence will therefore be estimated in the EHR cohort to enable comparisons with the trial and investigate the extent to which this may have influenced differences in treatment effect. With the EHR data we do not know how many tablets a patient has taken or if a given prescription is filled by a patient. We will estimate the proportion of time covered by prescribing as a proxy measure for adherence; this proxy measure assumes that all prescriptions are filled and that a patient takes all tablets in the prescription. This measure of adherence is not expected to accurately estimate the adherence of a given individual but should give an idea of how adherent a patient is compared with others. Prescribing for AF in the UK is predominantly through GPs meaning prescribing information from other potential sources of treatment should not be missing. However, it is possible that a patient's first prescription may be issued in hospital and treatment prescribed during any periods of hospitalisation will not be recorded in a patient's EHR leading to missing exposure data.

We will calculate the proportion of days covered (PDC) over a patient's time when on prescribed treatment as a measure of adherence. PDC will be estimated using patient prescription data including the total number of tablets prescribed, daily dose, and number of days on treatment (derived date of last dose – index date +1). This method of estimating adherence cannot easily be used for warfarin due to daily dose being poorly recorded in EHR; in a sample of CPRD Gold warfarin prescription records many patients had dose recorded with noninformative text such as “take as directed”. Depending on the quality of the prescription data warfarin adherence may instead be estimated by looking at patient adherence to other long-term daily medications as a proxy for warfarin adherence; the reliability of this measure would then be explored by comparing this proxy measure in the apixaban users with the PDC calculated directly using the apixaban prescription data.

For warfarin patients INR control will be assessed as a measure of adherence. We will look at INR values to calculate percent Time INR in Therapeutic Range (TTR) where the therapeutic range is 2.0 to 3.0 inclusive. Proportion of time in each INR interval will be calculated using Rosendaal's method. INR is influenced not only by patient adherence to the drug but also by other factors such as diet, alcohol intake, and drug interactions. The ability of a patient to comply with the lifestyle adjustments necessary to maintain INR control on a given warfarin dose may be considered as factors of warfarin treatment adherence. Patient INR control can therefore be used as a measure of overall warfarin treatment regime adherence.

We will perform a supplementary analysis comparing time to event while on treatment in patients deemed to have adequate proportion of time on therapeutic dose (adherent). We will also perform an exploratory subgroup analysis by INR TTR using TTR categories based on the TTR distribution.

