##### Date of last dose (all objectives)

The date of last dose will be estimated using the subject's date of prescription, number of tablets prescribed, and daily dose. Where there are missing values for the number of tablets prescribed or daily dose suitable values will be used to replace these, for example by substituting with the median or modal value. To allow for stockpiling of tablets and less than 100% adherence we will add 30 days after the apparent end of treatment when deriving date of last dose.

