##### **Missing Prescription Data**

Treatment may be initiated in secondary care meaning the first prescription of patients newly initiating treatment is missing. To account for these potentially missing first prescriptions we will perform a sensitivity analysis where those newly initiating treatment are assumed to have a missing earlier prescription and therefore assigned an earlier derived index date. Patients who are hospitalised may also have prescriptions issued in secondary care leading to treatment gaps seen in their primary care prescription data. The primary analysis using the Prescribed Population will not be affected by such gaps as patient time is included until the patient is censored or experiences an event regardless of treatment gaps. The supplementary analysis using the On-treatment Population and the safety analysis censor at derived date of last dose and may therefore miss events whilst a patient was on treatment in hospital. We will investigate the occurrence of hospitalisation around treatment discontinuation and assess the potential impact on the results of such missed events by performing a sensitivity analysis with different extended derived dates of last dose (extending the final period to 60 or 90 days after the final prescription estimated end).

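### The PDC denominator includes the 30 days added to the date of last dose, so apixaban adherence is understated, most of all in patients treated briefly

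*Protocol*

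**What the plan says.** Section O of the protocol fixes three things that bear on each other.

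- **Date of last dose.** It is estimated from prescription date, tablets and daily dose, and then "we will add 30 days after the apparent end of treatment when deriving date of last dose". The reason given is stockpiling and imperfect adherence. The addition applies to all objectives.
- **PDC.** Under Sensitivity analyses, "PDC will be estimated using patient prescription data including the total number of tablets prescribed, daily dose, and number of days on treatment". The last of these is spelled out as "number of days on treatment (derived date of last dose – index date +1". The protocol adds that "this proxy measure assumes that all prescriptions are filled and that a patient takes all tablets in the prescription", and that PDC "should give an idea of how adherent a patient is compared with others".
- **Use of adherence.** A supplementary analysis is planned "comparing time to event while on treatment in patients deemed to have adequate proportion of time on therapeutic dose (adherent". It gives no numerical cut-off and does not name the adherence measure.

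For warfarin, "This method of estimating adherence cannot easily be used for warfarin due to daily dose being poorly recorded in EHR". Adherence to other long-term medicines may be used as a proxy, its reliability being judged in apixaban users against their PDC. INR time in therapeutic range (TTR) is also assessed. Section Q, Missing Prescription Data, plans a sensitivity analysis "extending the final period to 60 or 90 days after the final prescription estimated end".

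**The concern.** The 30 days enter the denominator of PDC and have no counterpart in the numerator, which is built from tablets and daily dose. Nothing in the protocol removes them for PDC. On the protocol's own premise that every prescribed tablet is taken, uninterrupted supply ought to score 1, but the formula cannot return 1 for on-time supply of any length.

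The shortfall depends on duration of treatment, so it is not a constant that cancels when patients are compared. Three planned uses are exposed:

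- the ranking of patients by adherence;
- the comparison with trial adherence, which is meant to help explain any difference in treatment effect from ARISTOTLE;
- the check of the other-medicine proxy against apixaban PDC.

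A fourth use, choosing the adherent patients for the supplementary comparison, is exposed if PDC is the measure used there for apixaban.

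That comparison has a second difficulty, which does not come from the 30 days. PDC is calculated over the whole time on treatment, which is also when on-treatment events are counted. Membership of the subset therefore depends on what happens after the index date.

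**Working it through.** The protocol states no PDC value or cut-off, so there is no figure to reproduce. The check is arithmetic on its two definitions.

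**Inputs.** D is the number of days of uninterrupted, on-time supply (tablets divided by daily dose). The addition is 30 days (Date of last dose). Days on treatment equal derived last dose minus index date plus 1 (Sensitivity analyses).

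**Formula.** Derived last dose = index + (D − 1) + 30. Days on treatment = D + 30. Hence PDC = D/(D+30).

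| Days supplied, D | Calculation | PDC as defined |
|---|---|---|
| 28 | 28/58 | 0.483 |
| 56 | 56/86 | 0.651 |
| 84 | 84/114 | 0.737 |
| 120 | 120/150 | 0.800 |
| 365 | 365/395 | 0.924 |
| 730 | 730/760 | 0.961 |

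If the end of supply is counted as index + D, the denominator is D + 31 and the values fall slightly (28/59 = 0.475).

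**Ranking.** A patient supplied for 56 of 56 days scores 0.651. A patient supplied for 600 of 730 days has a true coverage of 600/730 = 0.822 and scores 600/760 = 0.789. The fully covered patient ranks below the one with gaps.

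**Cut-off.** With perfect supply, D/(D+30) ≥ c requires D ≥ 30c/(1−c). The protocol gives no c, so these are assumed values:

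| Assumed cut-off c | Minimum days of supply |
|---|---|
| 0.50 | 30 |
| 0.70 | 70 |
| 0.80 | 120 |
| 0.90 | 270 |
| 0.95 | 570 |

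If the 60- or 90-day extension were also carried into PDC, a cut-off of 0.80 would need 60 × 0.8/0.2 = 240 or 90 × 0.8/0.2 = 360 days.

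**Early refills.** Suppose 28-day packs are issued every 26 days, all tablets are counted, and the end date is taken from the last prescription. Then n packs give 28n/(26n + 32). This is 140/162 = 0.864 at 5 packs, 448/448 = 1.00 at 16 and 560/552 = 1.01 at 20. The ceiling is exact for on-time supply only, and without a cap PDC can exceed 1.

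**Illustration of the selection effect.** A simulation made every patient perfectly supplied in 28-day packs. The assumed rates per 100 person-years were 1.6 for events, 3.5 for death and 10 or 30 for stopping. It also assumed that 30% of events end prescribing and that the cut-off is 0.80. Between 4% and 10% of patients were classed as non-adherent. The event rate among those kept was 1.54 to 1.56, against 1.60 overall. In the first 90 days it was 1.10 to 1.14, against 1.60 to 1.62.

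**After correction.** With the denominator ending at the estimated end of supply, PDC = D/D = 1.00 at every duration under on-time supply. The two patients above score 1.00 and 0.82, in the right order.

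**The case against.** The strongest reply is that the arithmetic is right but its reach is short. No cut-off is stated, and a cut-off may properly be left to a statistical analysis plan. The adherent-patient analysis does not name PDC. Overlapping supply and any cap are unspecified, and early refills can offset the 30 days. The ceiling is already 0.92 at one year, and the protocol itself says PDC is not expected to be accurate for an individual. All of this stands, and it limits the consequences. It does not remove the error, because both definitions are explicit and conflict with the assumption stated beside them.

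A reader might also infer more than the protocol supports:

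- **That adherent apixaban patients have 120 days of guaranteed treated survival.** They do not. Supply counts days prescribed, so it guarantees survival only to the last issue. Two 60-day prescriptions, at index and on day 60, give D = 120 and PDC 0.80, yet the patient may die on day 61. The 120 days also rests on an assumed cut-off of 0.80.
- **That early events are dropped by construction.** PDC runs to the derived last dose and does not stop at the event. A patient with a non-fatal stroke on day 40 who stays on apixaban for two years scores 730/760 = 0.96 and is kept. Only events that end prescribing early are lost, and the illustration had to assume how many do.
- **That the 30 days cause the selection bias.** Selecting on adherence observed during follow-up conditions on the future with or without them. The 30 days add a duration-dependent ceiling on top.

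**Conclusion.** The PDC rule is wrong as written. For on-time supply it returns D/(D+30), so apixaban adherence is understated by about half at 28 days (0.48), by a fifth at 120 days (0.80) and by 8% at a year (0.92). This distorts the ranking of patients, the comparison with trial adherence and the check of the warfarin proxy against PDC.

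The effect on who counts as adherent is conditional. It assumes that PDC is the selection measure for apixaban, and its size depends on a cut-off the protocol does not give: 30 to 570 days of perfect supply across 0.50 to 0.95. Under the assumed rates and a cut-off of 0.80, the illustrated effect on the event rate is small over the whole of follow-up and marked in the first 90 days.

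Selection on adherence measured over the same period as the events is a separate weakness of that supplementary analysis, and correcting the denominator does not cure it.

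No primary or secondary outcome analysis and neither validation criterion uses PDC. The point is worth correcting before analysis but does not threaten the main conclusions.

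**What to change.** **PDC.** End the denominator at the estimated end of supply, or at censoring if that comes sooner, before the 30 days are added. Cap PDC at 1. Keep the 30 days, and the 60- and 90-day extensions, for on-treatment censoring only. The cost is one formula.

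**Supplementary adherent-patient analysis.** State the adherence measure and cut-off. Classify adherence in a fixed early window and start time at risk at its end, among patients still event-free and under follow-up, or treat adherence as time-varying. Re-check covariate balance in the selected subset, because selecting after 1:1 matching need not preserve it. The cost of the fixed window is that events within it are lost from this analysis only, so the length of the window is a trade-off to be justified.

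**TTR.** Keep the exploratory subgroup analysis by TTR, which bears on the INR-control question raised in the validation section.

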#### **o Censoring**

##### Index date

The index date for the EHR cohort will be the date of the patient's first prescription of apixaban or warfarin (for objectives 1 and 2), or for objective 3 first prescription of apixaban, warfarin, rivaroxaban, or dabigatran on or after the date the patient first met the eligibility criteria for the trial in the treatment period of interest

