##### Treatment Switching and Discontinuation

[figure not shown]

As the primary analysis accounts neither for treatment switching nor for treatment discontinuation and does not capture that these may be unfavourable outcomes both the proportion of patients discontinuing treatment and time to treatment discontinuation will be tabulated by prescribed treatment.

o Regression model

Hazard ratio (apixaban/warfarin) comparing the event rate (%/yr).

Interpretation: This estimand targets the treatment-policy effect of treatment initiation of apixaban vs initiation or continuation of warfarin on the time to first stroke or systemic embolism.

All time to event endpoints will be analysed using a Cox proportional hazards model including treatment group as a covariate and prior warfarin/VKA status (experienced, naïve).

Point estimates and two-sided 95% CIs for HR will be constructed for the outcome.

o Validation of Observational Results Against Aristotle Data

In Objective 1 alone we will validate the findings from our primary analysis against ARISTOTLE by determining whether results of the EHR analysis are compatible with the ARISTOTLE trial results. The ARISTOTLE trial demonstrated superiority of apixaban over warfarin for the primary endpoint (HR 0.79, 95% CI 0.66-0.95). The treatment effect seen with the EHR data may be weaker than that seen in ARISTOTLE.

A subgroup analysis looking at the outcomes of the EU patients in ARISTOTLE showed a smaller treatment difference with the estimate for HR below 1 but upper limit of the CI crossing 1 for the primary efficacy endpoint and death: HR for stroke/SE = 0.92 (95% CI = 0.56; 1.52), HR for all cause death = 0.89 (95% CI = 0.68; 1.18). It was suggested in the European Medicines Agency (EMA) Assessment Report that the smaller treatment effect seen in the EU patients could be due to better INR control in the warfarin arm of the EU subgroup (median TTR 68.93%). This study could provide additional evidence on this point. Since all the patients in our cohort are from the UK the results can be compared with the results from the ARISTOTLE patients in the EU.

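### The exploratory subgroup analysis by INR TTR splits on a post-index measure that only the warfarin arm has, so hazard ratios by TTR category can differ even when TTR does not modify the treatment effect

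*Protocol*

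**What the plan says.** The last paragraphs of the sensitivity analyses in section O deal with INR control. The measure belongs to one arm: "For warfarin patients INR control will be assessed as a measure of adherence". It is calculated by interpolation ("Proportion of time in each INR interval will be calculated using Rosendaal's method"), with 2.0 to 3.0 as the therapeutic range. The protocol justifies reading it as adherence: "Patient INR control can therefore be used as a measure of overall warfarin treatment regime adherence". It also acknowledges other influences: "INR is influenced not only by patient adherence to the drug but also by other factors such as diet, alcohol intake, and drug interactions".

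Two analyses follow. One is a supplementary analysis "comparing time to event while on treatment in patients deemed to have adequate proportion of time on therapeutic dose (adherent"). The other is the subgroup analysis: "We will also perform an exploratory subgroup analysis by INR TTR using TTR categories based on the TTR distribution".

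Baseline is fixed elsewhere in section O: "The index date for the EHR cohort will be the date of the patient's first prescription of apixaban or warfarin". Section N takes matching variables at first dose or from the latest earlier record. The interpretation paragraph under the regression model describes the comparator as patients who start or continue warfarin. Under the validation against ARISTOTLE, the protocol reports the suggestion that better INR control explains the weaker EU result (HR 0.92) and adds: "This study could provide additional evidence on this point".

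**The concern.** A subgroup analysis of a treatment effect needs a variable that is defined at or before baseline and can be assigned in both arms. On-study TTR meets neither condition. It exists only under warfarin, and as an adherence measure it describes what happened after the index date.

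Three things follow.

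- Matching balances the whole warfarin arm against the whole apixaban arm on baseline values. A third of the warfarin arm selected on its later course is not balanced against anyone.
- Anything that both worsens TTR and raises stroke risk makes low-TTR warfarin patients a higher-risk group and high-TTR patients a lower-risk one, whether or not TTR itself matters.
- TTR over a short follow-up is noisier and, in new starters, lower. An outcome event shortens the period in which TTR is measured, so category membership depends partly on the outcome.

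At stake is the reading of the TTR result. A gradient with more apixaban benefit at low TTR would look like support for the INR-control explanation that the protocol mentions, and the plan as written could not tell a real gradient from a false one.

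**Working it through.** The protocol gives no figure for this analysis, so there is none to reproduce. The check asks what HRs by TTR third would appear if TTR did not modify the effect.

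**Check 1: shared cause, in closed form.** Assumptions, none from the protocol: true HR 0.85 for everyone; warfarin hazard proportional to exp(0.5U - 0.125), with U a standard normal frailty; TTR on a normal scale with correlation r to U and no causal effect on the outcome; each warfarin third compared with the mean hazard of the whole apixaban arm.

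Weighting by exp(0.5U - 0.125) shifts the mean of TTR by 0.5r. With third cut-points at -0.431 and +0.431, the relative warfarin hazards are:

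- low third: 3 × Φ(-0.431 - 0.5r)
- high third: 3 × [1 - Φ(0.431 - 0.5r)]
- middle third: 3 minus the other two

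The HR in each third is 0.85 divided by the relative hazard.

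| r | Relative warfarin hazard, low / middle / high | HR, low / middle / high |
|---|---|---|
| 0 | 1.00 / 1.00 / 1.00 | 0.85 / 0.85 / 0.85 |
| -0.2 | 1.111 / 0.995 / 0.893 | 0.76 / 0.85 / 0.95 |
| -0.4 | 1.226 / 0.981 / 0.792 | 0.69 / 0.87 / 1.07 |

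For r = -0.2, low third: 3 × Φ(-0.331) = 3 × 0.3704 = 1.111, and 0.85/1.111 = 0.76. At r = 0 the false gradient vanishes, so this mechanism needs the correlation.

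**Check 2: simulation at the planned size.** From the protocol: about 9,000 per arm and a 5-year cap. Assumed: event rate 1.5% per year (1.0% and 2.0% gave the same pattern), 15% per year censoring, half the warfarin arm naive, mean TTR 0.67 with between-patient SD 0.10, and monthly INR noise. The true HR is 1.00 throughout and TTR has no effect. TTR is taken over each patient's follow-up, and each warfarin third is compared with the whole apixaban arm in a Cox model (300 runs). The last column is the low-versus-high contrast within the warfarin arm.

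| Mechanism | HR, low / middle / high | Contrast p<0.05 |
|---|---|---|
| Neither | 0.93 / 1.18 / 0.92 | 3% |
| TTR 0.25 lower in first 3 months for naive patients | 0.81 / 1.18 / 1.05 | 62% |
| Shared cause, log-HR 0.3 and TTR -0.04 per SD | 0.85 / 1.16 / 1.02 | 35% |
| Shared cause, log-HR 0.5 and TTR -0.06 per SD | 0.76 / 1.16 / 1.17 | 96% |
| Stronger shared cause plus initiation dip | 0.68 / 1.19 / 1.33 | 100% |

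The first row shows the follow-up-length effect alone: short follow-up pushes patients into the outer thirds. All three HRs are wrong, but low and high do not differ. A low-versus-high difference needs a shared cause or an initiation effect.

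**Is either mechanism plausible from the protocol itself?** The INR paragraph names diet, alcohol and drug interactions as influences on INR. Section F describes intensive INR checking at initiation until the patient is in range, and the comparator mixes starters with continuing users.

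**Do the remedies work under the same null?**

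- A 6-month landmark with both arms restarted there removes the follow-up-length and initiation artefacts (1.00/1.00/1.00). It leaves the shared-cause artefact: 0.93/1.00/1.07 with the moderate cause and 0.85/1.02/1.20 with the stronger one, with the contrast significant in 22% and 81% of runs.
- Splitting both arms on TTR predicted from baseline covariates gives HRs of 0.99 to 1.02 in every third and scenario, with low-versus-high differences significant in 4% to 8% of runs.

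**The case against.** The best counter-argument is that the flawed design is partly supplied by the critic. The protocol does not state the TTR window, the apixaban comparator for each category, or the adjustment, and such details often sit in an SAP, which is not shown here. Matching is 1:1, so the analysts could keep matched pairs or adjust for baseline covariates. This stands in part: either step would remove the part due to measured shared causes. It would not remove unmeasured causes or selection on follow-up length. The two simulated scenarios without any confounder (0.93/1.18/0.92 and 0.81/1.18/1.05) show what can remain when there is nothing to adjust for. The criticism concerns the stated choice of subgroup variable, not missing detail.

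It is also fair that the sizes rest on assumed correlations, that the moderate shared cause gives a non-monotone pattern, and that section P promises discussion of residual confounding in general. That promise does not address conditioning on TTR.

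Three stronger readings are tempting, and the protocol does not support them.

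- A reader might infer that this subgroup is the planned evidence on the EU result. The protocol ties that question to comparing the overall UK result with the EU patients of ARISTOTLE; it assigns the TTR subgroup no such role.
- A reader might infer that the adherent-patient analysis necessarily uses proportion of days covered in one arm and TTR in the other. The protocol leaves open a warfarin proxy based on other long-term medicines, which could be calculated in both arms.
- A reader might infer that the analysis is bound to show the INR-control pattern. Without a shared cause or an initiation effect, low and high thirds did not differ.

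**Conclusion.** The point holds as a defect in the choice of subgroup variable. TTR as planned exists in one arm and is measured after index, so HRs by TTR category are not estimates of effect modification.

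That the measure is post-index is inferred from its use as a measure of adherence to the warfarin regime. Continuing users may have earlier INRs, but the protocol does not restrict TTR to those.

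The direction of the false gradient, with a larger apparent apixaban benefit at low TTR, follows if poor TTR and stroke risk share causes or if TTR is low after initiation; the protocol's own text makes both plausible. The size is not known from the document. Across the shared-cause assumptions in Check 1 it runs from 0.76/0.85/0.95 to 0.69/0.87/1.07 around a true 0.85.

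The consequence is limited. The analysis is labelled exploratory and enters neither of the two validation criteria, so the primary estimate and the decision to extend the method are unaffected. The harm is that its result could be misread as evidence on INR control. The adherent-patient analysis has a related problem only if different post-index measures define adherence in the two arms.

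**What to change.** Replace the individual on-study TTR categories with a modifier defined before index in both arms, and estimate the treatment-by-TTR interaction. Any of these would serve:

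- practice-level TTR among warfarin patients, assigned to patients of both arms in that practice;
- TTR predicted from baseline covariates, calculated for both arms;
- pre-index TTR among warfarin-experienced patients, where it is available in both arms.

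Report individual on-study TTR descriptively, with no treatment-effect claim by category. A landmark window alone is only a partial remedy. For the adherent-patient analysis, state which measure defines adherence and use the same one in both arms.

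The cost is a change of wording and one derived variable, using INR data already planned. The downsides are real: practice-level and predicted TTR are blunter than individual TTR, and pre-index TTR covers only part of the cohort and is exposed to the channelling that section P acknowledges. Only the baseline-predicted version was simulated here.
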